### Trial audit and management

5.10

Someone external to the SCIMITAR-SA research team in each country will conduct monthly site visits using standardised checklists to verify adherence to the protocol, SOPs, and documentation standards. A lead investigator will complete at least one scheduled monitoring visit per country, with unscheduled visits by trial data coordinators if data quality or compliance concerns arise or if logistical issues require on-site resolution.

The Programme Management Group (PMG), comprising all study investigators, will meet monthly to oversee delivery, analysis, and dissemination. An Independent Advisory Board (IAB), consisting of experts in tobacco control, mental health, or global health research chaired by an external independent expert, will meet twice in the first year and annually thereafter. The IAB may recommend halting the trial if new evidence indicates harm or benefit, though early benefits alone will not stop recruitment.

### Progression criteria to a full trial

5.11

Progression from feasibility to the full trial will be guided by the Independent Advisory Board (IAB) using a “traffic light” framework.

**Green (proceed):** ≥80% recruitment within the target period, ≥80% retention at seven months (<10% difference between arms), and ≥80% completeness of primary outcome data (self-reported smoking status with biochemical verification).

**Amber (proceed with amendments):** Recruitment, retention, or data completeness of 50–79%, or minor procedural issues requiring adjustment.

**Red (review required):** <50% recruitment or retention, >16% difference between arms, or <50% outcome data availability.

Acceptability and feasibility of trial procedures and intervention delivery will also inform progression, assessed qualitatively through feedback from participants, TDAs, mental-health staff, and research teams.

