**At seven months follow up,** all measures from the four-month assessment and BPRS will be repeated, and an additional salivary sample will be collected to biochemically verify abstinence. We will operationalise the biochemically verified continuous abstinence from all tobacco products using the global Russell Standard of sustained and verified quitting [50]. For those who report using tobacco products on no more than 5 occasions during the cessation period (duration between the target quit date (for intervention group) or 30 days post-randomisation (for the control group) and the seven month follow up time point) at the seven-month follow-up, biochemical verification will be carried out through salivary cotinine and Anabasine testing through LC-MS (ACM Global Laboratories, UK for Bangladesh and Pakistan & Laboratory of the Department of Clinical Psychopharmacology and Neurotoxicology for India). Cotinine level <15 ng/ml will be used to identify biochemically verified abstinence), whereas those who self-report continuous abstinence but have cotinine levels above the threshold will be identified as tobacco users. Biochemically verified tobacco abstinence at seven months is included as an exploratory outcome to assess the feasibility of collecting cessation outcome data, including biochemical verification, and to inform outcome selection, measurement procedures, and sample size estimation for a future definitive trial.

Follow-up assessments at four and seven months post-randomisation will be considered on time if completed within a one-week window before or after the scheduled date. RAs will begin contacting participants one week prior to, and for up to three weeks after, each due date, making up to three phone calls per week at varying times and days to schedule the assessment. Instances of delayed follow-up will be documented and reviewed after the feasibility phase to refine procedures for the main trial. If the four-month data are missed, efforts will still be made to obtain information at the seven-month follow-up.

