## Outcomes

5

The study will report on the following feasibility outcome measures to address the research questions for the trial:i)Recruitment, retention, acceptability1.Recruitment rates, assessed as the number of participants eligible, consenting and randomised, out of those screened.2.Reasons for ineligibility/non-participation/non-consent of participants where provided.3.Retention in the study, assessed as the number of participants randomised who are successfully followed up at four and seven months post randomisation with details of withdrawals and loss to follow-up where available.4.Qualitative feedback from research staff, health facility staff and trial participants on trial processesii)Intervention Delivery1.Retention in intervention reported as the total number of sessions attended out of the total number of sessions offered.2.Review of participant session records held by TDAs3.Qualitative feedback from TDAs, mental health facility staff and trial participants on delivery, implementation and receipt of the SCIMITAR-SA intervention.iii)Data completion1.Completeness of data for baseline assessments, outcome measures for the definitive trial and data on health resource use at four and seven months.2.Data completeness of self-reported and biochemically verified continuous abstinence from all tobacco products at seven months.

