### Sample size

5.1

The trial will recruit 100 participants across the six facilities (10 from the two Karachi facilities and 20 from the remaining four) which will allow estimation of recruitment (50%) and retention (80%) to within a 7% and 8% margin of error.

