### Statistical analysis

5.2

No formal statistical comparisons will be undertaken. Continuous variables will be summarised using means and standard deviations, or medians and interquartile ranges where data are skewed, while categorical variables will be reported as frequencies and percentages. A CONSORT [51] flow diagram will illustrate participant progression through screening, recruitment, intervention delivery and follow-up. The numbers screened, eligible, consenting, and recruited will be summarised, including reasons for ineligibility or non-consent where available. For intervention participants, session attendance will be reported, and recruitment and retention rates by trial arm will be presented with 95% confidence intervals(CIs). Data completion rates for each outcome measure will be summarised by trial arm at baseline and follow-up, along with reasons for withdrawal and any reported adverse events. All analyses will be conducted using Stata (version to be confirmed).

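### The Green/Red rule for primary outcome completeness asks for biochemical verification, but only participants claiming abstinence are verified, so the percentage does not measure whether verification worked

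*Protocol article*

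**What the plan says.** Section 5.11 (Progression criteria to a full trial) sets three numerical conditions for Green. The third is "≥80% completeness of primary outcome data (self-reported smoking status with biochemical verification". Amber covers 50–79%, and Red is "<50% outcome data availability", a phrase that no longer mentions verification. No denominator is given for either.

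Section 4 (Baseline and follow-up data collection procedures) says who is verified at seven months: "For those who report using tobacco products on no more than 5 occasions during the cessation period", the cotinine and anabasine assay is carried out. Participants who report more use have no assay, by design. Table 1 and the opening of the seven-month paragraph list a saliva sample without naming a subgroup, so collection may be wider than testing.

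Section 5 (Outcomes) lists as a feasibility outcome "Data completeness of self-reported and biochemically verified continuous abstinence from all tobacco products at seven months", again without a denominator. Research question 2 in section 1.2 asks whether data can be collected for the future primary outcome, biochemically verified continuous abstinence at seven months.

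**The concern.** The completeness criterion is the decision rule closest to research question 2. It joins two things with different denominators: self-report, which every participant can give, and an assay result, which only those claiming abstinence can have. Merged into one percentage, the answer depends on a counting choice that the article does not state, and the same data could be rated Red or Green. If that choice is made after the data are in, the threshold no longer serves its purpose. On the more natural way of counting, the many continuing users, for whom no assay is needed, dilute any failure in saliva collection, transport or testing.

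A smaller point of wording: the criterion speaks of smoking status, whereas the trial enrols smokeless-only and dual users and the outcome covers every tobacco product.

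**Working it through.** **Inputs from the article.** "The trial will recruit 100 participants across the six facilities", so 100 randomised. Green retention is "≥80% retention at seven months (<10% difference between arms". Completeness is Green at 80% or more, Amber at 50–79%, Red below 50%. The confidence level is 95% (section 5.2).

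**Input not in the article.** The share of followed-up participants who claim abstinence, *q*. It is an assumption here, shown mainly over 10% to 30%.

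**The plan's own figures.** The sample size section states only precision: "which will allow estimation of recruitment (50%) and retention (80%) to within a 7% and 8% margin of error". With the margin 1.96 × √(p(1−p)/n):
- recruitment, p = 0.5, n = 200 (the number implied by 100 recruited at 50%): 6.9%, stated as 7%;
- retention, p = 0.8, n = 100: 7.8%, stated as 8%.

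Both are reproduced. No figure is given for the completeness criterion.

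**Reading 1: each participant needs self-report and an assay.** Maximum completeness out of randomised = retention × *q*, even with perfect sampling.

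| Retention | q = 10% | q = 20% | q = 30% |
|---|---|---|---|
| 80% | 8% | 16% | 24% |
| 90% | 9% | 18% | 27% |

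All are Red. Leaving Red at 80% retention needs *q* = 0.50/0.80 = 62.5%. Green needs *q* = 100% at 80% retention, or 0.80/0.90 = 89% at 90%. On this reading the figure tracks claimed quitting, not data collection.

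**Reading 2: self-reported users count as complete, claimants only if assayed.** If no assay succeeds at all, completeness out of randomised = retention × (1 − *q*).

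| Retention | q = 5% | q = 10% | q = 20% | q = 30% |
|---|---|---|---|---|
| 80% | 76% Amber | 72% Amber | 64% Amber | 56% Amber |
| 90% | 85.5% Green | 81% Green | 72% Amber | 63% Amber |
| 95% | 90.2% Green | 85.5% Green | 76% Amber | 66.5% Amber |

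In counts: 90 followed up, 10 claimants, none assayed gives (90 − 10 + 0)/100 = 80%, Green with nothing verified. Partial failure behaves the same way: 95 followed up, 20 claimants, 5 assayed gives (75 + 5)/100 = 80%, Green with 25% verified. Complete failure of verification is never Red in this table. If the denominator is those followed up, completeness with no assays is 1 − *q*, which is Green for any *q* up to 20%.

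**Reading 3: the assay is counted only among claimants.** This would measure verification directly, but the article does not say it.

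**Precision after a split.** Status known out of 100 randomised, at 80%: ±7.8 points. Valid assay among claimants, at 80%: √(0.16/10) × 1.96 = ±24.8 points with 10 claimants, and √(0.16/20) × 1.96 = ±17.5 with 20.

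**The case against.** The strongest reply is that Reading 1 is strained. Under the Russell Standard as section 4 applies it, a participant who reports continued use is a user on self-report alone, and the primary outcome is complete without an assay. The parenthesis in section 5.11 may only name the data sources, and the Red rule does not mention verification. A reader might infer that the criterion is always Red, or that it must be either unreachable or empty. The article does not support that: the Red result depends on an assumed *q* as well as on that reading, and Reading 3 would be workable.

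A reader might likewise infer that Reading 2 gives Green whenever verification fails. It does not. On the randomised denominator, Green with no assays needs high retention and few claimants; at 80% retention and 10% claiming the result is 72%, Amber.

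It can also be said that failed saliva collection would show elsewhere. Section 5 lists completeness of verified abstinence as an outcome, section 5.2 summarises completion by measure and arm, and the Board is guided by the traffic light and also weighs qualitative evidence. That is true, and the failure would not be invisible. But descriptive reporting does not repair the decision rule. The full protocol may define the denominator, yet the article prints the rule itself, and that rule does not match its own testing procedure.

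Universal saliva collection, if intended, would make sample completeness measurable in everyone. The criterion asks for verification, however, and testing is restricted.

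One objection changes the remedy. A hard 80% gate on about 10 claimants would be erratic: with a true success rate of 80%, the chance of at least 8 of 10 is 0.302 + 0.268 + 0.107 = 0.68, so an adequate process would miss Green about one time in three.

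**Conclusion.** The concern holds in a limited form. The completeness criterion in section 5.11 does not fit the verification procedure in section 4, and neither natural way of counting over all participants answers research question 2. Needing an assay for each participant caps completeness at 8–27% for 80–90% retention and 10–30% claiming abstinence. Counting self-reported users as complete lets continuing users carry the figure: complete failure of verification gives Amber over much of the plausible range, and Green when retention is about 90% or more and claimants are about 10% or fewer. These sizes rest on the assumed share claiming abstinence, for which the article gives no value. Section 5.11 needs correcting before seven-month data are seen.

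**What to change.** Split the completeness criterion in section 5.11 into two components.

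1. Tobacco-use status for all products known at seven months, out of all randomised, with the existing 80% and 50% cut-points.
2. Valid cotinine/anabasine result, out of those reporting no more than five occasions of use. Give this to the Independent Advisory Board as a separate count and percentage with a 95% CI, and judge it against the same cut-points as guidance rather than as a mechanical gate.

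Replace smoking status with tobacco-use status in the criterion, and use the same two denominators for the matching outcome in section 5.

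The cost is a rewording, with no new data. The downside is that the second component is imprecise (about ±25 points with 10 claimants, ±18 with 20), which is why it should inform the Board rather than bind it.

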### Dissemination of trial findings

5.12

Findings will be published in peer-reviewed journals following SCIMITAR-SA's publication policy and ICMJE guidelines [60], and presented at international meetings on tobacco control, psychiatry, and global health. Summaries will be shared with participants, caregivers, and communities through reports and local dissemination by Community Advisory Panels (CAPs) in each country. Wider visibility will be achieved via media, the SCIMITAR-SA website(https://www.impactsouthasia.com/scimitar-sa/) and official LinkedIn (Scimitar South Asia), Instagram(@Scimitar_SA),and Threads (@Scimitar_SA) accounts, especially around World Mental Health and World No Tobacco Days.

## Discussion

6

The SCIMITAR-SA feasibility trial will address a critical evidence gap by evaluating the feasibility of a culturally relevant behavioural intervention to support tobacco cessation among individuals with SMI in South Asia. This population faces high rates of tobacco dependence and significant barriers to cessation, yet tailored, evidence-based support remains limited. The study's participant-centred approach integrates cessation support for smokers, smokeless tobacco (SLT) users, and dual users, combining behavioural intervention with optional NRT (where available as part of routine care) delivered within existing mental health services.

A major strength of the study lies in its multi-country implementation across diverse health-system contexts in Bangladesh, India, and Pakistan, using consistent, validated tools and a robust data-collection framework. The inclusion of qualitative process-evaluation components adds depth to understanding contextual barriers and facilitators of implementation. Moreover, the focus on integrating cessation support into routine psychiatric care highlights the feasibility of sustainable delivery models.

However, as a feasibility study with a modest sample size, it is not powered to detect significant differences in effectiveness outcomes. Other limitations include potential variability in NRT availability across sites, challenges in retaining a highly clinically vulnerable population, and possible under-reporting of tobacco use due to social desirability bias. Despite these constraints, SCIMITAR-SA provides an essential foundation for a definitive trial and strengthens the evidence base for integrating tobacco cessation into mental health care in low- and middle-income settings.

### Protocol amendments

6.1

The current version of the trial protocol (Version 3.0, dated August 20, 2025) incorporates revisions recommended by the trial sponsor and the Trial Management Team (PMG and IAB) to date. All proposed amendments are reviewed with the Chief Investigators before submission to the University of York Research Governance Committee (HSRGC) for formal consideration. The Committee determines whether each amendment is classified as major or minor, following institutional guidance. Minor amendments are implemented upon notification, whereas major amendments require prior approval from the respective national ethics committees in each participating country before implementation.

## Availability of data and materials

Not applicable.

## Ethics approval and consent to participate

The feasibility trial protocol has been approved by the Health Sciences Research Governance Committee (HSRGC) at the University of York (Ref: HSRGC/2024/626/E: SCIMITAR-SA), National Research and Bioethics Committees in Bangladesh (National Research Ethics Committee (NREC) functioning under Bangladesh Medical Research Council (BMRC)), (Ref: BMRC/NREC/2025-2027/128), Health Ministry's Screening Committee (HMSC) operated by the Department of Health Research/Indian Council of Medical Research (ICMR)) and the Screening Committee for Research Proposal (SCRP), Department of Health and Family Welfare, Ministry of Health and Family Welfare, Government of India (Ref: F.No P- 29010/19/2025-DMCell), Ethics Committee (Behavioural Science Division) of National Institute of Mental Health and Neurosciences, Bengaluru, India, (Ref: NIMHANS/47th IEC (BEH.SC.DIV.)/2024), National Bioethics Committee for Research (NBC-R) at Health Research Institute, National Institutes of Health (NIH)) in Pakistan (Ref: 4-87/NBCR-1145/24-25/1422), and Institutional Research & Ethics Forum (IREF), Rawalpindi Medical University (RMU), Rawalpindi, Pakistan (Ref: 810/IREF/RMU/2024). Any amendment to the protocol will be submitted for approval to the same ethics governing bodies in respective partner countries. The informed consent to participate in the feasibility trial will be obtained directly from the patient(s).

## Consent for publication

Not applicable.

## Data Availability

No data was used for the research described in the article.
